### Safety reporting

Unanticipated or adverse events will be monitored and reported to ensure participant safety. Serious adverse events will be reported upon discovery at the clinical center. Participants returning to clinic at different time point(s) not pre-determined; those found to have elevated AFP or hepatic nodules that are not during the study visits; and other events during patient follow-up, i.e. cirrhosis decompensation, incidental findings of hepatic mass detected not by the study, clinic presentation outside of study follow-up date ranges, inconclusive findings of hepatic nodule by imaging and liver biopsy will be monitored, reviewed, and reported.

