### Study schedule and assessments

Figure 2 depicts the study schema. The study is planned for five years. Individuals with a liver mass ≥ 1 cm in diameter, elevated AFP (≥ 9 ng/mL), and/or elevated GALAD score (≥ -0.63) will be scanned with dynamic contrast-enhanced MRI, and a diagnosis of HCC will be made by LiRADS-5. Additionally, those who do not exhibit abnormal imaging findings, elevated AFP titer, and/or elevated GALAD score will obtain a dynamic contrast-enhanced MRI annually for five years to assess for HCC. In Vietnam, the study sites and the funds to be received for the study will be used for conducting all the tests and MRIs. National health insurance will not be used. In Saudi Arabia, national health insurance will cover the participants’ tests and MRIs.

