**Fig. 2 Fig2:**
[figure not shown]
Study Schema. Patients with chronic liver diseases from hospital database of the participating sites will be screened and invited for enrollment if eligible. Next, we prospectively survey the eligible cohort of patients at risk for HCC (i.e. patients with advanced fibrosis or compensated cirrhosis and irrespective of cirrhosis etiologies), using semi-annual abdominal ultrasound and GALAD Score for five years. During the 5-year follow-up, individuals with a liver mass ≥ 1 cm in diameter and/or elevated GALAD score (≥ -0.63) will be scanned with dynamic contrast-enhanced MR,I and a diagnosis of HCC will be made by LiRADS assessment (LiRADS-5). Additionally, those who do not exhibit abnormal imaging findings and/or elevated GALAD score will obtain a dynamic contrast-enhanced MRI annually for five years to assess for HCC

During the 5-year time frame, we anticipate at least 80 (approximately 16 each year if 1% incidence x five years for both cohorts in Vietnam and Saudi Arabia) or as many as 320 (64 per year if 4% incidence x five years for both cohorts in Vietnam and Saudi Arabia) incident HCC cases given the high HCC incidence rate in Vietnam and Saudi Arabia. With the range of 80 to 320 anticipated HCC cases, we will have 90% to 99% power, respectively, to detect a meaningful difference in the cases vs. control (more on sample size calculation below). We will compare sensitivity for early HCC detection (primary outcome measures), false-positive results, and resultant diagnostic evaluation.

By leveraging the prospective cohort, we will establish a biorepository of longitudinally collected biospecimens from patients with fibrosis/cirrhosis to be used as a reference set for future research. Clinical, laboratory, and imaging data, urine, and plasma biospecimens are from participants for up to five years; data are collected only from participants who maintain the absence of evidence of HCC on imaging and/or biopsy. Biospecimens and associated de-identified clinical data from participants enrolled in this study will be stored in Vietnam for participants from Vietnam and in Saudi Arabia for participants enrolled from Saudi Arabia.

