### Schedule of activities

Data will be collected during screening (initial visit) and at semi-annual intervals thereafter (a maximum of ten visits). Schedule of activities (Table 1) displays the data collection schedule for screening and follow-up.

**Table 1 Tab1:** Schedule of activities

Procedures	Screening/baseline (Visit 1)	Study Visit 2	Study Visit 3	Study Visit 4	Study Visit 5	Study Visit 6	Study Visit 7	Study Visit 8	Study Visit 9	Final Study Visit 10
Informed consent	X									
Demographics	X									
Home address/Phone number	X	X	X	X	X	X	X	X	X	X
Medical history	X	X	X	X	X	X	X	X	X	X
Collect and archive serum (15 mL blood, 50 mL urine)	X	X	X	X	X	X	X	X	X	X
Concomitant medication review	X	X	X	X	X	X	X	X	X	X
Physical exam (including height and weight)	X	X	X	X	X	X	X	X	X	X
Vital signs	X	X	X	X	X	X	X	X	X	X
Height	X									
Weight	X	X	X	X	X	X	X	X	X	X
Waist circumference	X	X	X	X	X	X	X	X	X	X
Performance status	X	X	X	X	X	X	X	X	X	X
Handgrip strength measurements	X	X	X	X	X	X	X	X	X	X
Hematology	X	X	X	X	X	X	X	X	X	X
Serum chemistry	X	X	X	X	X	X	X	X	X	X
Adverse event review and evaluation		X	X	X	X	X	X	X	X	X
Radiologic/Imaging assessment (Abdominal Ultrasound and/or cross section imaging if triggered)	X	X	X	X	X	X	X	X	X	X
Dynamic contrast-enhanced CT or MRI	X		X		X		X			X
Fibroscan	X									X
Complete Case Report Forms (CRFs) that have clinical data and events	X	X	X	X	X	X	X	X	X	X

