### Follow-up visits

Semi-annual follow-up visits will be scheduled at 22 to 26-week intervals after enrollment. Each visit has an ideal date for a visit, a lower window date (opening date for the window), and an upper window date (closing date for the window). The dates for a specific participant are specified on their visit time windows sheet. In addition to the activities in Table 1, new procedures and forms are to be completed at each of the follow-up visits (at 6, 12, 18, 24, 30, 36, 42, 48, and 54 months) are:Follow-up medical history (medication changes, key events or interventions, surgeries)Hospital admissions, new diagnoses of co-morbidities, complications of liver disease (variceal bleeding, ascites, edema, hepatic encephalopathy), liver cancer, other cancer, diabetesPhysical examinationAbdominal US and AFPLaboratory data (hematology, glucose, insulin, clinical chemistry, hepatic panel, HbA1c, lipid profile)Blood collection for plasma bankingDocumentation of any additional liver biopsies performed

Additionally, annually, each study participant will obtain a dynamic MRI with contrast to evaluate for liver cancer.

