### Outcome ascertainment and study exit definitions

Time of positive surveillance: latest date of visit with lab resultsCriteria for outcome assessment: elevated GALAD score and/or suspicion of liver tumor on ultrasound, whichever comes firstDate of detection of liver tumor ≥ 1 cm in size on dynamic contrast-enhanced MRI or confirmation of HCC on biopsyOutcome captured if multiphase MRI with contrast is not needed when GALAD score is less than the cut-off and ultrasound findings are normal.Tumor of any size and quantity will be recorded.Person-years of follow-up time: calculated for each participant from one year after the enrollment date to the event date (indication for multiphase MRI with contrast; HCC diagnosis; date of loss to follow-up, or end of study, whichever comes first).Time to event: from entry in the study to the date of liver tumor detection on multiphase MRI with contrast or on the date of biopsy with HCC confirmation.GALAD score and ultrasound: within four weeks of the visit with indicationLoss to follow-up: 12 months of last clinic encounter with no study visitsEnd of study: completion of the last visit or procedure shown in Table 1 or when a patient develops HCC and then subject to the local management protocol (above)

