### Statistical methods

Bootstrap resampling technique will be used to account for repeated measures to estimate standard errors and confidence intervals. Only MRI nearest to the time of GALAD, US and/or AFP evaluation will be included in the analysis. For time-to-event data, we will use the Cox proportional hazards regression model with covariates tailored to the hypothesis under investigation. For hypotheses involving repeated measurements, events, counts, or other discrete responses, we will use either of two approaches: (1) generalized linear models with generalized estimating equations with robust variance estimation to account for the clustering, or (2) multilevel generalized linear mixed models with random coefficients to account for within-patient clustering as well as other sources of variations like clinic effects.

We will include a random intercept for each hospital site to account for variability by facility. Stratified analyses will be presented for p for interaction < 0.2. Demographic and clinical characteristics will be summarized with proportions and median (minimum–maximum) with no calculation of p-values as this is a non-randomized study. Age at liver disease diagnosis and sex will be accounted for in all analyses. Other confounders of interest include interval follow-up and insurance coverage, whereas age and gender are already controlled in the GALAD (gender, age, etc.) score calculations. All statistical analyses will be performed in SAS 9.4 (or R or another statistical software package with equivalent capabilities).

Baseline descriptions of patients with the standard of care (US and AFP) vs. GALAD score will be compared to each other. Other baseline demographics, biochemical lab results, MRI results, Fibroscan, and abdominal US in the cohort will also be described.

The interim analyses will re-evaluate the performance of the GALAD cut-off score of -0.63 after year 2 of the study. The interim analyses will not be used to assess for study events (i.e., HCC cases), and thus there will be no plan to stop the study if there were no number of events (i.e. HCC cases).

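### Under the stated outcome and nearest-MRI rules, an HCC diagnosed between visits after a negative GALAD can drop out of the sensitivity denominator

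*Protocol article*

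**What the plan says.** All references are to the protocol article.

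- **Primary measure.** The text below Figure 2 states: "We will compare sensitivity for early HCC detection (primary outcome measures), false-positive results, and resultant diagnostic evaluation".
- **Verification of test-negatives.** Under Study schedule and assessments, participants with no abnormal imaging, no raised AFP and no "elevated GALAD score will obtain a dynamic contrast-enhanced MRI annually for five years to assess for HCC". Follow-up visits adds that "annually, each study participant will obtain a dynamic MRI with contrast to evaluate for liver cancer". The same section has liver cancer recorded as part of the interval history at every visit.
- **Outcome ascertainment and study exit definitions.** A GALAD above the cut-off or an ultrasound suspicious for tumour, whichever occurs earlier, is given as the criterion for outcome assessment. Another item, awkwardly worded, treats the outcome as captured with no contrast MRI needed when GALAD is below the cut-off and ultrasound is normal. Time to event runs from "entry in the study to the date of liver tumor detection on multiphase MRI with contrast or on the date of biopsy with HCC confirmation". A participant who develops HCC leaves the study.
- **Pairing of test and reference.** Statistical methods: "Only MRI nearest to the time of GALAD, US and/or AFP evaluation will be included in the analysis". The Abstract and Screening say the same.
- **Off-visit findings.** Safety reporting lists AFP rises and nodules found outside study visits, together with "incidental findings of hepatic mass detected not by the study, clinic presentation outside of study follow-up date ranges", as matters to be monitored, reviewed and reported. It neither excludes them from the HCC outcome nor says that they enter it.

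**The concern.** For a six-monthly surveillance test, a cancer that surfaces between a negative test and the next visit is the clearest kind of miss. It belongs in the sensitivity denominator as a false negative. Here one section closes test-negatives without MRI while others scan them yearly, the analysis keeps only one MRI per test, and off-visit masses are named only as safety matters. Sites and analysts could follow these rules faithfully and still never set such a cancer against the negative GALAD that preceded it. The quantity at stake is the primary measure. A participant who is sent to MRI because of a positive GALAD is likely to be diagnosed within the study, so cancers that surface elsewhere are more likely to be GALAD-negative at the last test.

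**Working it through.** **1. The plan's case count.** The text below Figure 2 says "we anticipate at least 80 (approximately 16 each year if 1% incidence x five years". Check: 1,600 × 0.01 = 16 a year, × 5 = 80. At 4%: 1,600 × 0.04 × 5 = 320. Both figures reproduce.

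**2. Scheduled MRI.** In Table 1 the row "Dynamic contrast-enhanced CT or MRI" is marked at Visits 1, 3, 5, 7 and 10. With follow-up visits at months 6 to 54, these are months 0, 12, 24, 36 and 54. The last gap is 54 − 36 = 18 months, which does not match yearly MRI.

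**3. The stated rules applied to four courses.**

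- *GALAD negative at month 6; diagnosed at another hospital at month 9 by MRI.* The month-9 MRI is 3 months from the test and the baseline MRI is 6 months away. If outside MRIs are admitted, the nearest-MRI rule gives a false negative, which is correct. If only study MRIs are used, the pairing is with baseline, because the participant exits at diagnosis and has no month-12 scan. Baseline MRI must be negative for enrolment, so the test is scored a true negative.
- *The same, but diagnosed by outside CT or biopsy only.* There is no month-9 MRI to pair. The nearest MRI is the negative baseline scan: a true negative.
- *GALAD and MRI both negative at month 12; HCC diagnosed at month 15.* The same-visit MRI is at gap zero and is always nearest. The month-12 GALAD is a true negative even if the month-15 diagnosis was by MRI. Unless a GALAD was drawn at diagnosis, the cancer is a case for no test.
- *Diagnosed and treated elsewhere; the participant does not return.* The follow-up visit that would record the cancer does not take place. After 12 months the participant is lost to follow-up, and one of the two analyses under Missing data removes such participants.

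The only test-timing window among the outcome definitions (four weeks) ties GALAD and ultrasound to an indicated visit. No maximum gap between a test and an MRI or diagnosis is stated.

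**4. Illustration of size.** The inputs are 80 cases (the plan's), true sensitivity *s* = 70% (assumed), and a share *f* of all cases omitted, all of them GALAD-negative at the last test (assumed). True positives = 0.70 × 80 = 56; misses = 24. Apparent sensitivity = 56 / (80 − 80*f*) = *s* / (1 − *f*).

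| Share omitted | Cases omitted | Apparent sensitivity | Excess |
|---|---|---|---|
| 0% | 0 | 56/80 = 70.0% | 0 |
| 5% | 4 | 56/76 = 73.7% | 3.7 points |
| 10% | 8 | 56/72 = 77.8% | 7.8 points |
| 15% | 12 | 56/68 = 82.4% | 12.4 points |

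With 320 cases (224 true positives) the percentages are the same: 224/304, 224/288 and 224/272. For scale, a simple binomial 95% half-width at 70% is 1.96 × √(0.7 × 0.3/80) = 10.0 points with 80 cases and 5.0 points with 320. More cases narrow the interval but leave the bias unchanged.

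**5. Direction.** If all 8 omitted cases had been GALAD-positive, the result would be (56 − 8)/72 = 66.7%, an understatement. There is no bias when the omitted cases are GALAD-positive in the same proportion as all cases: 10 omitted, 7 positive, gives 49/70 = 70%.

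**The case against.** The strongest reply is that the design already looks for cancers GALAD missed. Test-negatives have yearly MRI, liver cancer is recorded at every follow-up visit, a mass of 1 cm or more leads to MRI whoever found it, and the event date is not limited to study visits. This stands, and it disposes of the reading that outcome assessment begins only with a positive test. It does not cover a cancer diagnosed before the next scheduled scan. Recording the cancer or dating it for a Cox model also does not classify the preceding GALAD.

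A reader might infer that listing off-visit masses under safety reporting excludes them from the outcome. The section does not say so; an event can be both a safety report and an outcome.

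A reader might also infer that the error always favours GALAD. That is too strong. A GALAD-positive participant diagnosed elsewhere before the triggered MRI would, if dropped, lower apparent sensitivity.

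Two further replies deserve weight. An article may leave test-to-event pairing to the full protocol or analysis plan, so silence alone would be no finding. The point survives because rules that are stated can give the wrong classification. It can also be said that a GALAD negative beside a same-visit negative MRI was right on that day. That defends same-day accuracy, but the stated aim is performance in prospective surveillance for early detection, where a cancer soon after a negative test is a miss.

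**Conclusion.** The point holds in conditional form. The outcome-ascertainment section conflicts with the yearly-MRI text, and the nearest-MRI rule can pair a negative GALAD with an earlier or same-visit negative scan. An HCC diagnosed between visits can then be absent from the sensitivity denominator or counted as a true negative, and sensitivity could be overstated.

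The documents do not support the flat statement that sensitivity is overstated. They give neither an expected sensitivity nor a share of interval cancers. The range of 74% to 82% against a true 70% rests on four assumptions: the 70% itself, omission of 5% to 15% of 80 cases, all of these GALAD-negative, and none of them counted. If they are counted, the bias is zero. The illustration also uses all HCC as its denominator, whereas the primary measure concerns early HCC, so it shows the mechanism and is not a forecast.

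**What to change.** - Reconcile Outcome ascertainment and study exit definitions with Study schedule and assessments and with Follow-up visits on whether and when test-negatives are imaged, and reconcile Table 1 with both. Which schedule governs is for the sponsor.
- State in Outcome ascertainment, Safety reporting and Statistical methods that every HCC diagnosed from enrolment to the end of follow-up, by MRI, CT or biopsy and at any hospital, is an outcome event as well as any safety report.
- Pair each such HCC with the last GALAD, AFP and ultrasound before diagnosis, within a stated window, and count it as a false negative for each of those tests that was negative. For these cases this pairing overrides the nearest-MRI rule.
- Report interval cancers on a separate line.

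The cost is a wording change and retrieval of outside imaging or pathology for a few participants. The records release under Enrollment is worded for study laboratory results and imaging, and may need to be widened. Reported sensitivity may come out lower. The rule should be in place during follow-up, because outside reports not collected at the time may be unobtainable later.

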### Sample size

Two estimates were calculated for the sample size, assuming low (1%) and high (4%) annual incidence rates in the population with the highest risk for HCC. Assuming an annual incidence of 1%, 90% power and alpha of 0.05 during the 5-year follow-up period, we anticipate a 5-year incidence proportion of 0.05 (5*0.01). The sample size needed is 621 (each country). For a 4% annual incidence rate using the same assumptions, the sample size required is 119. To err on the conservative side, we aimed to recruit 800 per country (Vietnam and Saudi Arabia) to account for the loss to follow-up. These sample size calculations were performed in Stata 15.1 using the “sampsi” command.

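### The sample size and the 90–99% power rest on a comparison of HCC incidence, so power for the primary outcome, GALAD's sensitivity for early HCC, is not shown

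*Protocol article*

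**What the plan says.** The Sample size section takes HCC incidence as its only clinical input. For the low scenario it writes "Assuming an annual incidence of 1%, 90% power and alpha of 0.05 during the 5-year follow-up period", then "we anticipate a 5-year incidence proportion of 0.05 (5*0.01" (the bracket closes there), and concludes "The sample size needed is 621 (each country". For the high scenario: "For a 4% annual incidence rate using the same assumptions, the sample size required is 119". It names Stata's sampsi command and sets recruitment at 800 per country. It gives no sensitivity, specificity, precision target or comparator proportion.

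The text below Fig. 2, under Study schedule and assessments, expects 80 to 320 incident HCC cases over both countries and says "we will have 90% to 99% power, respectively, to detect a meaningful difference in the cases vs. control", referring forward to the sample size calculation. The next sentence reads "We will compare sensitivity for early HCC detection (primary outcome measures), false-positive results, and resultant diagnostic evaluation".

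Outcome measures defines the primary endpoint as the performance of GALAD at the −0.63 cut-off against LiRADS-5. Study design and the GALAD score section describe one observational cohort in which GALAD is added to routine ultrasound and AFP for everyone. Missing data says that the sample size allowed for up to 30% missing data or loss.

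**The concern.** The quantity that was sized is not the quantity the study sets out to estimate. Sensitivity is a proportion among participants who have HCC, so its information comes from the case count, not from 621 participants. A difference in HCC incidence also cannot be tested between cases and controls, because HCC status is what defines those groups.

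The power sentence stands directly before the sentence that names sensitivity as primary, so a reader will attach 90–99% to sensitivity. At the low incidence, an estimate with a wide interval could then be read as coming from a well-powered study, and all the more so if results are shown by country.

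**Working it through.** **1. Reproducing 621 and 119.**

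Inputs from the Sample size section: power 90%, alpha 0.05, first proportion 5 × 0.01 = 0.05 (low) or 5 × 0.04 = 0.20 (high). Not stated: the second proportion and whether the test is one- or two-sided. Doubling the first proportion, with a two-sided test, is tried here.

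Uncorrected size per group, with p̄ the mean of the two proportions and d their difference:

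m = [1.960 √(2p̄(1−p̄)) + 1.282 √(p₁(1−p₁) + p₂(1−p₂))]² / d²

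Continuity-corrected size: n = (m/4) [1 + √(1 + 4/(m d))]²

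- 5% vs 10%: m = (0.7301 + 0.4752)² / 0.05² = 581.1; n = 620.4, rounded up to **621**.
- 20% vs 40%: m = (1.2702 + 0.8105)² / 0.20² = 108.2; n = 118.02, rounded up to **119**.

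One rule gives both published figures. The alternatives do not: two-sided without correction gives 582 and 109; one-sided with correction gives 513 and 98. A one-sample test comes near only with arbitrary second values (about 0.083 and 0.327).

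**2. Where the stated power fits.**

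The same incidence comparison with 621 per group has 90.0% power for 5% vs 10% and over 99.9% for 20% vs 40%. The claimed 90–99% is compatible with that comparison, although the derivation of 99% is not shown.

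**3. The denominator for sensitivity.**

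| | Low (1%/year) | High (4%/year) |
|---|---|---|
| Both countries, 1,600 × 5 × rate | 80 | 320 |
| One country, 800 × 5 × rate | 40 | 160 |
| Both countries, less 30% | 56 | 224 |

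The last row assumes that cases are lost in proportion to participants. Counts are smaller still if only early-stage HCC enters the denominator.

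**4. Precision.**

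Half-width = 1.96 √(s(1−s)/cases), with an assumed sensitivity s = 0.70:

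- 80 cases: 1.96 √(0.21/80) = ±10.0 points; 320 cases: ±5.0.
- 40 cases (one country): ±14.2; 160 cases: ±7.1.
- 56 cases (80 less 30%): ±12.0; 224 cases: ±6.0.

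**5. Paired power.**

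If GALAD is compared with ultrasound/AFP in the same patients, the McNemar approximation with discordance π and difference d is

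power = Φ[(d√cases − 1.96√π) / √(π − d²)]

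Example: 80 cases, d = 0.15, π = 0.25 gives (1.342 − 0.980)/0.477 = 0.76, so Φ = 78%.

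The differences and the discordance range (π = 0.25 to 0.35) are assumptions; the protocol gives neither.

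| Difference in sensitivity | 80 cases | 320 cases |
|---|---|---|
| 10 points | 32–43% | 86–95% |
| 15 points | 62–78% | over 99% |
| 20 points | 87–96% | over 99% |

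With 56 cases, a 15-point difference has 47–62% power.

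**The case against.** The strongest reply is that the arithmetic is right and that a protocol article may leave the effect size to the full document. Both points are fair as far as they go. The numbers do reproduce, and a missing effect size alone would not be a finding. What remains is a printed power claim that refers to a calculation on a different quantity.

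A second reply is that an incidence contrast could have been meant. A Cox model for time to HCC is planned, and a doubling of incidence between GALAD-positive and GALAD-negative participants is conceivable. The text does not describe this, and 621 per group at a 1:1 split would need 2 × 621 = 1,242 per country against 800 planned. The fair statement is that the contrast is unstated, not that none could exist.

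Three stronger readings are tempting, and the protocol does not support them:

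- **Country is the comparison group.** The words after 621 can equally mean that this number is needed within each country.
- **The study lacks 90% power for sensitivity.** No comparator, margin or paired test is named. On the assumptions above, 80 cases give 87–96% power for a 20-point difference, and 320 cases do well even for 10 points. Power is undemonstrated, not shown to be absent.
- **GALAD and standard care are to be analysed as separate patient sets.** The sentence in Statistical methods, "Baseline descriptions of patients with the standard of care (US and AFP) vs. GALAD score will be compared to each other", is about baseline description. It is awkward, but it specifies no unpaired accuracy test.

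The 80 to 320 cases are also explicitly for both countries together, so the by-country figures show what country-level results could deliver. They do not refute a claim the protocol makes.

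**Conclusion.** The concern holds in this form: 621 and 119 are sized on 5-year HCC incidence, the 90–99% power does not follow for the primary outcome, and power for that outcome is not shown. It is a mismatch between the sizing basis and the endpoint, not an error of arithmetic.

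The incidence basis is explicit in the text. The two-group form and the comparators of 10% and 40% are inferred, but from two exact matches under one rule. The consequence is concentrated at the low incidence, where a 15-point difference would be detected with roughly 62–78% probability and the interval around a sensitivity of 70% would span about 20 points. At the high incidence the study would be well placed for differences of 15 points or more. These sizes depend on the assumed sensitivity, difference and discordance.

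**What to change.** In Sample size and in the text below Fig. 2, withdraw the 621/119 justification and the sentence claiming 90% to 99% power. Keep 1,600 participants. Justify that number by the expected 95% half-width for sensitivity and for specificity at both ends of the case range, pooled and by country, after the stated 30% loss.

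If GALAD is to be compared with ultrasound/AFP, name that comparison and give power for a within-patient paired test, with the assumed difference and discordance stated. The baseline sentence in Statistical methods needs at most a clearer wording.

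This is a change of text only, with no extra participants or procedures. The cost is that the stated figure becomes less favourable at the low incidence.
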